#### Attrition Analyses

To ensure the validity of findings, baseline characteristics of patients and caregivers who drop out of the study will be compared by study group. We will also summarize and compare reasons for attrition. If any differences are found, the appropriate covariance adjustments or propensity score stratifications will be employed in the primary analysis. To ensure the generalizability of our findings, we will also compare the baseline characteristics of those completing the study against those of subjects who drop out.

#### Primary Analytic Strategy

The primary effect of the intervention will be determined using data obtained at 10 weeks, and the sustained effect will be determined using data obtained at 14 weeks. Cross group comparisons will be made based on an intention-to-treat basis. We will also test the hypotheses with a longitudinal design by fitting a linear mixed-effects modelor a generalized linear mixed effects model to estimate effect averaged over 10 and 14 weeks, adjusting for potential within-person correlation and baseline values of the outcome variables [15].

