**Methods/Design:**

We describe the design and rationale of a randomized, controlled trial to assess the efficacy of 10 weeks of web-based caregiver alerts and tailored advice for helping a patient manage symptoms related to chemotherapy. The study aims to test the primary hypothesis that patients whose caregivers receive alerts and tailored advice will report less frequent and less severe symptoms at 10 and 14 weeks when compared to patients in the control arm; similarly, they will report better physical function, fewer outpatient visits and hospitalizations related to symptoms, and greater adherence to chemotherapy. 300 patients with solid tumors undergoing chemotherapy at two Veteran Administration oncology clinics reporting any symptom at a severity of ≥4 and a willing informal caregiver will be assigned to either 10 weeks of automated telephonic symptom assessment (ATSA) alone, or 10 weeks of ATSA plus web-based notification of symptom severity and problem solving advice to their chosen caregiver. Patients and caregivers will be surveyed at intake, 10 weeks and 14 weeks. Both groups will receive standard oncology, hospice, and palliative care.

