The current protocol describes an ongoing randomized trial designed to address these gaps in the literature by developing and evaluating an intervention that provides cancer patients and caregivers with the information they need to make effective management decisions, decrease symptom burden, and improve patient and caregiver outcomes. The study was funded by the VA Health Services Research and Development Service and began October, 2009. The trial will be completed in August 2013.

The intervention uses a Web-enabled program to alert caregivers of patients' symptoms and provide them with a framework for identifying problems, receiving structured advice, and following up to assist the patient in manage symptoms while receiving chemotherapy. Specifically, the intervention includes weekly, automated telephonic symptom assessment with self-management support calls to patients paired with Web-based caregiver alerts that include customized advice. The study will enroll 300 patients with solid tumors undergoing chemotherapy identified from two Department of Veterans Affairs (VA) outpatient oncology clinics. Patients are recruited along with an informal caregiver willing to play a limited role in assisting the patient with symptom management. The impact of the intervention will be evaluated relative to a control arm in which patients receive automated telephonic symptom assessments and self-management advice without any involvement of their identified caregiver. Thus this is one of the few rigorously designed interventions that tests the value added impact of engaging informal caregivers in symptom management for patients with cancer. Specific study hypotheses are as follows:

*Hypothesis 1a: Patients receiving automated telephonic symptom assessment and management advice, with Web-based feedback to inform and engage a caregiver, will report less frequent and less severe symptoms at 10 and 14 weeks when compared to patients receiving automated telephonic symptom assessment and management advice alone. Intervention-group patients will also report better physical function, fewer outpatient visits and hospitalizations related to symptoms, and greater adherence to chemotherapy*.

*Hypothesis 1b. The effect of the intervention on symptom severity, physical functioning, and utilization of services will be partially mediated by improved patient self-efficacy and actualized social support*.

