## Methods

The intervention's efficacy is being evaluated using a randomized, controlled trial among patients undergoing a course of chemotherapy at two Department of Veterans Affairs (VA) oncology clinics located in Ann Arbor, MI and Fargo, ND. Three hundred patients with solid tumors undergoing chemotherapy and reporting at least one core symptom at a moderate level are being assigned to either 10 weeks of weekly ATSA contacts or 10 weeks of weekly ATSA contacts plus caregiver alerts and access to the Cancer CarePartners website. The duration and intensity of the intervention is premised on past work suggesting that ATSA's benefits peak at 10 weeks [11].

The goal of the study is to determine if, when compared to a comparison group receiving ATSA alone, patients who receive ATSA and whose caregivers receive access to Cancer CarePartners will report: significantly less total symptom severity; and secondarily improved physical functioning, adherence to chemotherapy, and more appropriate utilization of health services at 10 weeks. The study also will determine whether caregivers provide more social support and report less caregiver burden and distress.

Patients and caregivers will be surveyed at intake, 10, and 14 weeks. Further, we will track patient participation with ATSA and (in the experimental arm) caregiver use of the Website and social support provided, allowing for indicators of intervention dose to be incorporated into our analyses. Finally, all patients will receive routine oncology, hospice, and/or palliative care.

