#### Hypothesis Testing

We will compare summed symptom scores at 10 weeks between the control and intervention groups using a multiple regression model. The model will include a dummy variable for study group assignment as the main independent variable and will be adjusted for baseline symptom scores. While we do not expect the groups to be unbalanced with respect to other potential predictors of the outcome, we will adjust for these if randomization is not fully successful. The parameter estimate of the group assignment dummy variable and its statistical significance will estimate and test for the outcome difference between the two study groups at week 10, adjusting for baseline values of the outcome. A similar approach will be used to test the intervention effect on secondary outcomes (namely physical functioning, service utilization, and chemotherapy adherence). To determine if there is maintenance of the intervention effects on each outcome, we will use a similar regression model using the corresponding measurements at week 14, and a longitudinal model for the outcomes at 10 and 14 weeks.

Our analytic approach for testing Hypothesis 2 will be similar to that described above. We will use multiple regression models to compare group differences in patient-reported social support scores as measured by the Inventory of Socially Supportive Behaviors at 10 weeks, adjusting for baseline values of the ISSB [38]. The model will include a dummy variable for study group assignment as well as the baseline value of the ISSB scores, and the parameter estimate of the dummy variable will estimate the intervention effect on caregivers at 10 weeks. A similar approach will be used to test the intervention effect on caregiver burden and distress.

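### The primary hypothesis is worded for 10 and 14 weeks but the primary effect is set at week 10, and the averaged 10/14-week test of the same hypotheses has no stated rank

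*Protocol article*

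**What the plan says.** The protocol article gives the timing of the primary question in several places.

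- **Abstract, Methods/Design.** The primary hypothesis is that patients of alerted caregivers "will report less frequent and less severe symptoms at 10 and 14 weeks when compared to patients in the control arm".
- **Background, Hypothesis 1a.** Intervention patients "will report less frequent and less severe symptoms at 10 and 14 weeks when compared to patients receiving automated telephonic symptom assessment" (that is, the calls and advice with no caregiver feedback).
- **Methods, opening section.** The study goal covers total symptom severity and then the secondary outcomes, and the sentence closes with "more appropriate utilization of health services at 10 weeks". No 14-week goal is given there.
- **Primary Analytic Strategy.** This section begins: "The primary effect of the intervention will be determined using data obtained at 10 weeks, and the sustained effect will be determined using data obtained" in the week-14 survey. The same paragraph then says "We will also test the hypotheses with a longitudinal design by fitting a linear mixed-effects" model, and gives its purpose as "to estimate effect averaged over 10 and 14 weeks, adjusting for potential within-person correlation and baseline values of the outcome variables".
- **Hypothesis Testing.** The week-10 summed score is compared by baseline-adjusted regression. To judge whether effects are maintained, the plan uses a week-14 regression "and a longitudinal model for the outcomes at 10 and 14 weeks".
- **Missing Data.** The models take both follow-up assessments together as repeated outcomes. The listed terms are an intervention indicator, the baseline outcome value and other covariates.
- **Sample Size Calculation.** The level 0.05 appears here and nowhere else, for a two-sided t-test of the primary outcome. No week is named.

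**The concern.** The hypothesis and the analysis that is to decide it do not name the same time point. A trial that succeeds at week 10 and fails at week 14 confirms the primary effect as Primary Analytic Strategy defines it, but not the hypothesis as the abstract and Hypothesis 1a word it.

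The averaged mixed-model effect makes this harder to settle. One section introduces it as a further test of the hypotheses, and another uses the longitudinal model to judge maintenance. An average over both weeks cannot isolate maintenance, because an effect at week 10 alone can make it significant. In practice it is another test of efficacy.

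The Missing Data section could also change which contrast is reported. With 25% attrition expected, missing values are close to certain. A longitudinal model with one intervention indicator and no group-by-time term estimates the averaged effect, not the week-10 effect.

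At stake is which contrast answers the primary question when they differ. If that is left until the results are known, the data can influence the choice.

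**Working it through.** **1. The plan's own figure.** The inputs in Sample Size Calculation are a difference of 0.33 SD, two-sided 0.05, 80% power and 112 per arm.

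- Required n per arm = 2(1.960 + 0.842)² / 0.33² = 15.70 / 0.1089 ≈ 144.2, so 145. The stated 112 is not reproduced.
- Power at 112 per arm: 0.33 × √(112/2) = 2.470, and Φ(2.470 − 1.960) = 0.695. The noncentral t gives 0.691.
- A one-sided 0.05 test would need 114 per arm, but the text says two-sided. Baseline adjustment would bring the need to about 112 if the baseline correlation were near 0.47: 144.15 × (1 − 0.47²) = 112.3. The article does not state that correlation.
- Attrition: 224 / 0.75 = 298.7, so 299, which agrees with 300.

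The sample size is a separate matter. It enters here only because the power figures below use 112 per arm without baseline adjustment, where the week-10 test has 69.5% power.

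**2. Set-up.** Let Z10 and Z14 be the week-10 and week-14 test statistics with correlation r, and let the averaged statistic be Zavg = (Z10 + Z14) / √(2 + 2r). This assumes equal variances and complete data at both weeks. The article gives no r, so 0.3 to 0.9 is an assumption. Each test is taken as two-sided at 0.05, which is also an assumption for the week-14 and averaged tests. Results are from 2,000,000 simulated draws. In the alternative, the true effect is 0.33 SD at both weeks, so each single-week statistic has mean 2.470.

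| r | No effect: at least one of three significant | Average significant, week 10 not | At least one but not all three significant | Weeks 10 and 14 both significant |
|---|---|---|---|---|
| 0.3 | 0.105 | 18.6% | 37.6% | 52.2% |
| 0.5 | 0.097 | 14.1% | 30.7% | 55.1% |
| 0.7 | 0.086 | 9.4% | 22.9% | 58.5% |
| 0.9 | 0.071 | 4.3% | 12.7% | 63.3% |

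The second column applies only if any of the three results may be claimed as confirmation. If week 10 alone decides, the error rate is 0.05 for every r.

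**3. Power of the literal both-weeks reading.** Success at both weeks has 52-63% power, against 69.5% for week 10 alone. If the stated 80% at week 10 is granted instead, the both-weeks power is 67%, 69%, 71% and 73% for r = 0.3, 0.5, 0.7 and 0.8. It is lower than the week-10 power either way.

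**4. If the average displaces week 10 and the effect fades.** Suppose the effect is 0.33 SD at week 10 and half that, 0.165 SD, at week 14. The averaged effect is (0.33 + 0.165)/2 = 0.2475 SD, a different quantity from the week-10 effect. Week 10 is then significant while the average is not in 12.7%, 15.5%, 18.5% and 21.9% of trials for r = 0.3, 0.5, 0.7 and 0.9. The reverse occurs in 6.4%, 3.1%, 0.9% and about 0%. So the displacement can also work against the intervention.

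**The case against.** The best defence is that the plan already ranks its analyses. Primary Analytic Strategy says "The primary effect of the intervention will be determined using data obtained at 10 weeks" and gives week 14 the sustained effect. Hypothesis Testing carries this out, and the Methods goal is set at 10 weeks. Hypothesis 1a also goes on to physical function, service use and adherence, so it reads as a broad research hypothesis and not as a rule requiring success on every element.

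Most of this stands. A reader might infer that three tests, each at 0.05, can decide the trial, and that the false-positive rate is therefore nearly doubled. The article does not support that. The level 0.05 is given once, in the sample size paragraph. No section says that a week-14 or averaged result may establish the primary hypothesis. The article likewise states no rule that both weeks must succeed.

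A condensed article may also leave multiplicity detail to an analysis plan that is not shown. That answers a complaint about missing alpha rules. It does not answer the inconsistencies in the text itself: the hypothesis and the primary effect name different time points, the longitudinal model has two roles, and the model described for missing data lists no term that would yield a week-10 contrast.

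**Conclusion.** The point holds as a conflict of wording and of model specification. Week 10 is the intended primary time point, but the stated primary hypothesis does not match it, the averaged test has no rank, and the model in Missing Data could replace the week-10 contrast with the average.

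The intended reading leaves type I error at 0.05. The figure of about 0.07-0.11 is conditional on treating any of the three results as confirmation, with each test at 0.05 and a correlation of 0.9-0.3 that the article does not give.

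The practical size is how often the contrasts part ways. With 112 per arm, no baseline adjustment and a true 0.33 SD effect at both weeks, the average succeeds where week 10 fails in about 4-19% of trials over the same correlations. The literal both-weeks reading has less power than the week-10 test throughout. This should be settled before results are known, but it does not call the design into question.

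**What to change.** - **Abstract and Hypothesis 1a.** State the primary hypothesis for summed symptom severity at 10 weeks. Move 14 weeks to a secondary hypothesis of sustained effect.
- **Primary Analytic Strategy and Hypothesis Testing.** State that only the baseline-adjusted week-10 group coefficient, at two-sided 0.05, decides the primary hypothesis. Label the week-14 comparison secondary and the averaged mixed-model effect supportive.
- **Missing Data.** Add a group-by-time term so that the longitudinal model yields the week-10 contrast. State that, where this model is used because of missing values, its week-10 contrast takes the deciding role.

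Testing week 14 only after a significant week 10 is one acceptable option, not a requirement.

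The cost is a few sentences and one model term, with no new data and no change in sample size or in the level of the week-10 test. The downside is that a week-14 or averaged result can no longer rescue a failed week-10 test.

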#### Missing Data

When missing values occur, we will determine whether missingness is random or associated with patient or caregiver characteristics using standard regression models. As long as we do not observe any bias in patterns of dropout or missing data (see attrition analysis above), we will use regression techniques allowing for missing at random. Models will include 10 and 14 week assessment data as longitudinal outcome values, an intervention effect indicator, and baseline values of the outcome variable and other covariates as fixed independent variables. If the analyses indicate that missingness depends on unobserved outcome values(, we will account for missing data using a pattern mixture model [43]. This technique allows the use of data from all participants (not just completers) and provides an unbiased intervention effect estimate.

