### Intervention Components

#### Automated Telephonic Symptom Assessment (ATSA)

ATSA is an automated telephonic system that calls patients at home to collect their symptom ratings via responses to recorded queries using their telephone's touchtone keypad. ATSA's questions consist of items from the MD Anderson Symptom Inventory modified for the telephone and validated in prior cognitive-behavioral studies of symptom management [15,18-21]. The ATSA system was developed based on prior research showing that patients with cancer and other serious chronic diseases can and will report reliable information during automated assessment calls, and that such calls may improve their self-care and health outcomes [22-25]. The duration and intensity of the intervention is premised on past work that suggesting that ATSA's benefits peak at 10 weeks [26].

The ATSA system calls patients weekly and asks them to rate the frequency and severity of eight core symptoms: pain, distress, fatigue, insomnia, nausea, poor appetite, dry mouth, and constipation. The choice of core symptoms is based on prior work by Given and colleagues showing that among patients undergoing chemotherapy, 85% experience at least one of these symptoms [11]. Patients are asked how many days during the last week they have experienced each symptom. When patients report a frequency of once per week or greater, the ATSA prompts patients to rate the severity of that symptom on a scale of 0 to10.

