#### ATSA

ATSA tracks call attempts, call outcomes (completed vs. incomplete), and reported symptom scores. The number of completed calls relative to call attempts will be used to describe patient uptake of the intervention as well as the dose received.

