### Data Analysis

#### Sample Size Calculation

Testing the primary outcome using two sided t-testing will require at least 224 dyads (patients and caregivers) to complete the study (112 per arm). This sample size affords 80% power to detect a difference as small as 0.33 standard deviations in mean summed symptom severity (Hypothesis 1) and social support (Hypothesis 2) between arms using 0.05 as the level of significance. This consistent with standards for clinical relevance and those seen in similar interventions [26,42]. Moreover, this sample size is sufficient to accommodate longitudinal analyses with repeated measures. To account for 25% attrition (consistent with prior trials of ATSA) and ensure that 112 dyads in each group are available for analysis, the goal is to enroll 300 dyads in the trial [26].

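### For the symptom survey outcome, patients with no follow-up survey fall out of the stated models, while their stored weekly ATSA ratings of the same eight symptoms have no role in handling missing data

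*Protocol article*

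**What the plan says.** The primary test is set out under Hypothesis Testing: "We will compare summed symptom scores at 10 weeks between the control and intervention groups using a multiple regression model", adjusted for the baseline score. Under Primary Analytic Strategy a mixed model is added "to estimate effect averaged over 10 and 14 weeks". The Missing Data section lists what the missing-at-random models contain: "Models will include 10 and 14 week assessment data as longitudinal outcome values". A term for study arm is also included, and the remaining terms enter as "baseline values of the outcome variable and other covariates as fixed independent variables". If missingness is judged to depend on unobserved outcomes, a pattern mixture model replaces them. The section says that this model draws on every participant and gives an unbiased effect.

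The intervention section says: "The ATSA system calls patients weekly and asks them to rate the frequency and severity of eight core symptoms". Severity is rated 0 to 10 for any symptom present in the week. The Comparison group and Intervention group sections give these calls to both arms for 10 weeks, and the scores are stored. Under Data Sources, "ATSA tracks call attempts, call outcomes (completed vs. incomplete), and reported symptom scores". The stated uses are call counts for uptake and dose, call data for usability, and weekly safety review of the scores. No section gives the severity scores a part in the outcome or missing-data analysis.

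The sample size section allows for loss: "To account for 25% attrition (consistent with prior trials of ATSA").

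**The concern.** Patients on chemotherapy may leave because their symptoms worsen. If so, two patients with the same baseline score can have quite different week-10 prospects, and the weekly calls recorded after randomization carry part of that difference. A model that knows only baseline treats the leaver as if they would have followed the patients who stayed.

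The arm comparison suffers mainly if the link between symptoms and exit differs by arm. That is possible here, because only intervention caregivers are prompted to act when a symptom reaches severity four. The error could then shrink a real effect or produce an apparent one. Baseline adjustment and propensity strata built on baseline characteristics, the remedies named under Attrition Analyses, do not use the symptom course after randomization.

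**Working it through.** **1. The plan's attrition figure.** 224 / (1 - 0.25) = 298.7, so 299. Per arm, 112 / 0.75 = 149.3, so 150, or 300 in total. The stated 300 reproduces. Planned loss is 300 x 0.25 = 75 patients. This is an upper bound for exit before week 10, because it counts dyads not completing the study.

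**2. Who enters which model.**

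| Surveys completed | Week-10 regression | Longitudinal model | Chart-based outcomes |
|---|---|---|---|
| Weeks 10 and 14 | in | in | in |
| Week 10 only | in | in | in |
| Week 14 only | out | in | in |
| Neither | out | out | can be in |

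Baseline is a covariate and not an outcome row, so the last group adds nothing to the likelihood for survey outcomes. Chart review is done also after withdrawal or death, so utilization and chemotherapy adherence can still include these patients.

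**3. The pattern mixture fallback.** An arm's week-10 mean is the sum over patterns of (share of pattern x mean in pattern). With 25% in the no-survey pattern, the mean is 0.75 x (mean with data) + 0.25 x (mean without data). With outcomes only at weeks 10 and 14, nothing observed estimates the last term. It needs intermediate data or an identifying restriction, and neither is stated.

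**4. Size, by simulation.** From the protocol: 150 per arm, 25% exit, effect -0.33 SD, ten weekly scores, and week 10 regressed on arm and baseline. Assumed: SD 1, effect building linearly to week 10, random-intercept share 0.4, AR(1) 0.7 or 0.85, exit log-odds rising by 1 per SD of the previous weekly score where linked, all calls completed up to exit, and ATSA measuring the survey score without error. The alternative predicts week 10 within arm from baseline and the weekly scores, then fits the same regression. There were 3000 runs per cell, and the two values are for AR(1) 0.7 / 0.85.

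| Exit linked to symptoms in | True effect | Stated model | Using weekly scores |
|---|---|---|---|
| Neither arm | -0.33 | -0.330 / -0.334 | -0.330 / -0.335 |
| Both arms equally | -0.33 | -0.315 / -0.319 | -0.328 / -0.333 |
| Control arm only | -0.33 | -0.246 / -0.243 | -0.332 / -0.332 |
| Control arm only | 0 | +0.089 / +0.090 | +0.003 / +0.001 |
| Intervention arm only | 0 | -0.089 / -0.090 | -0.004 / -0.001 |

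In the third row the bias is 0.33 - 0.246 = 0.084 to 0.33 - 0.243 = 0.087, about a quarter of the effect (0.084 / 0.33 = 25%). Estimates had an SD of about 0.11 to 0.13. Variance fell by about 4 to 8% when exit was unrelated to symptoms and was otherwise about the same (ratios 0.98 to 1.04). The leavers held about 300 to 316 unused weekly records, roughly 4 each (300 / 75 = 4).

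A separate simulation (1500 replicates, AR(1) 0.8) gave -0.31 with equal links and -0.25 with a control-only link. Using the weekly scores it gave -0.33 and -0.32.

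**5. Less extreme assumptions** (AR(1) 0.8, control slope 1, equal exit rates in the two arms).
- Intervention slope 0.5: stated model -0.29 at 25% exit and -0.31 at 15%.
- Intervention slope 0.75: -0.31 and -0.32.
- Intervention slope 0 at 15% exit: about -0.28 to -0.29.
- Intervention slope 0 at 25% exit, with ATSA a noisy measure of the symptom driving exit: using the weekly scores gives about -0.29 to -0.30 at reliability 0.7 and -0.27 to -0.28 at 0.5, against a true -0.33.

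**The case against.** The strongest reply is that a journal article leaves the choice of auxiliary variables to the analysis plan, that ATSA is listed as a data source, and that nothing forbids its use. This stands in part: silence about auxiliaries would not by itself be a fault. But the article goes further. It fixes the outcome rows and promises an unbiased estimate from all participants, which the described model cannot deliver for patients without follow-up. Nor would entering ATSA scores among the other covariates help: leavers would still have no outcome row, and adjusting for symptoms after randomization would absorb part of the effect.

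The plan also limits loss. Leaving the study on hospice entry is optional, shortened interviews and up to 10 contact attempts are provided, and reasons for attrition are compared by arm. These lower the risk and may reveal differential exit, but do not correct for it.

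Several stronger readings are tempting, and the documents do not support them.
- That leavers add nothing to any outcome model: chart-based outcomes can include them, and week-14-only patients enter the longitudinal model.
- That the all-participants sentence misdescribes the missing-at-random models: it refers to the pattern mixture model.
- That ratings exist right up to exit: calls can be missed, or suspended in hospital.
- That a quarter of the effect will be lost: this needs exit driven by symptoms in one arm and wholly unrelated to them in the other, and no section points to that.

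**Conclusion.** The point holds for the survey-based symptom outcome and should be acted on as a cheap improvement. The stated models condition missingness on less than the trial records, and the assurance attached to the fallback is not met as described. Expected bias is small under ordinary conditions: about 0 to 0.02 SD when exit is unrelated to symptoms or equally related in both arms. The range of 0.08 to 0.09 SD, about three quarters of a standard error (0.09 / 0.12 = 0.75), needs the strong one-arm link at about 25% exit before week 10. Intermediate assumptions fall between. All these sizes rest on assumed correlations and exit models, and the protocol cannot supply them. The gain is mainly in bias; precision hardly changes.

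**What to change.** - Keep the week-10 survey score as the primary outcome and keep the baseline-adjusted regression.
- Multiply impute missing week-10 and week-14 scores from baseline and the available weekly ATSA eight-symptom sums, counting a symptom not reported in a week as zero. Impute within arm, because the relation between ATSA and survey scores may differ when a caregiver sees the ratings.
- Report the completer result alongside.
- State how deaths before week 10 are handled, as an explicit estimand choice. Restricting to patients alive at week 10 conditions on an event after randomization, and this should be said if that route is taken.
- Remove the claim of an unbiased estimate from all participants, or qualify it by naming the intermediate data or restriction that identifies the no-follow-up pattern.

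The cost is analysis work only, since the scores are already stored. The downside is that ATSA is an automated keypad call that can be missed or suspended, while the outcome is an interview. It should serve as a predictor and not replace the outcome, and it reduces the bias without necessarily removing it.
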